### 6.5.4 Evaluation of Other Clinical Abnormalities

For other adverse events, participants should promptly record the start and end dates of the event, as well as any treatment measures taken, on the daily report card. These events will be graded according to the criteria in Appendix 2. For clinical abnormalities not covered in Appendix 2, the severity will be assessed using the grading standards provided in Table 8.

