| Bilirubin: Elevated
due to factors with
normal liver function      | 1.1~1.5×ULN                                                                               | 1.6~2.0×ULN                                                                                                            | 2.0~3.0×ULN                                                     | >3.0×ULN                                     |
| Bilirubin: Elevated
due to factors with
abnormal liver
function | 1.1~1.25×ULN                                                                              | 1.26~1.5×ULN                                                                                                           | 1.51~1.75×ULN                                                   | >1.75×ULN                                    |
| CK and Isoenzymes                                                        | 1.25~1.5×ULN                                                                              | 1.6~3.0×ULN                                                                                                            | 3.1~10×ULN                                                      | >10×ULN                                      |
| Troponin                                                                 | 1.25~1.5×ULN                                                                              | 1.6~3.0×ULN                                                                                                            | 3.1~10×ULN                                                      | >10×ULN                                      |
| Urine                                                             |                                                                                           |                                                                                                                        |                                                                 |                                              |
| Glucose (mmol/L)                                                         | ≤15                                                                                       | 15.1~20                                                                                                                | 20.1~30                                                         | >30                                          |

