| DNA Vaccine | Injection Site
Erythema                   | Diameter <1.5 cm                                                      | Diameter 1.5–3 cm                                                                         | Diameter >3 cm                                                       | Gangrene or
exfoliative dermatitis                                                                        |
|                    | Injection Site and
Blisters and
Ulcers | Blisters or ulcers at injection site, diameter <1 cm                  | Blisters or ulcers at injection site, diameter 1–2 cm, heals within 2 weeks               | Blisters or ulcers at injection site, does not heal for over 2 weeks | Necrosis                                                                                                     |
|                    | Injection Site
Induration                 | Diameter <1.5 cm                                                      | Diameter 1.5–3 cm                                                                         | Diameter >3 cm                                                       | Gangrene or
exfoliative dermatitis                                                                        |
|                    | Injection Site
Papules                    | Diameter <1.5 cm                                                      | Diameter 1.5–3 cm                                                                         | Diameter >3 cm                                                       |                                                                                                              |
|                    | Injection Site
Pustules                   | Diameter <0.5 cm                                                      | Diameter 0.5–1 cm                                                                         | Diameter >1 cm, no tendency to heal for 2 weeks                      | Necrosis                                                                                                     |
|                    | Injection Site
Swelling                   | Diameter <1.5 cm, no impact on activity                               | Diameter 1.5–3 cm or impacts activity                                                     | Diameter >3 cm or restricts daily activities                         | Gangrene                                                                                                     |

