| Myalgia           | Does not affect daily activities                   | Tenderness in non-injection site muscles, slightly limits daily activities        | Severe muscle tenderness, severely affects daily activities                                                           | Severe symptoms, muscle necrosis, emergency or hospitalization |                                    |
| Arthralgia        | Mild pain, does not limit daily activities         | Moderate pain, slightly limits daily activities                                   | Severe pain, severely affects daily activities                                                                        | Hospitalization required                                       |                                    |
| Nausea            | Mild or transient, does not affect normal eating   | Affects normal eating                                                             | Unable to eat, requires outpatient IV fluids                                                                          | Hospitalization required                                       |                                    |
| Vomiting          | 1 episode in 24 hours                              | 2–5 episodes in 24 hours                                                          | >6 episodes in 24 hours or IV fluids required                                                                         | Requires hospitalization or alternative nutrition              |                                    |
| Diarrhea          | Mild or transient, 2–3 episodes/day, lasts <1 week | Moderate or persistent, 4–5 episodes/day, or diarrhea >1 week                     | >6 episodes/day, or bloody stools, orthostatic hypotension, electrolyte imbalance, requires >2L IV fluids in 24 hours | Hypotensive shock, requires hospitalization                    |                                    |
| Cough             | Transient, no treatment required                   | Paroxysmal cough, treatment effective                                             | Persistent cough, treatment ineffective                                                                               | Emergency or hospitalization                                   |                                    |

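### Annex 2 leaves some larger DNA-site lesions, and exactly six episodes of vomiting or diarrhoea, without a grade at the Grade 2/3 line, and one Grade 3 criterion outlasts the low-dose safety look

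*Protocol*

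**What the plan says.** Annex 2, DNA vaccine block, grades blisters and ulcers as follows: Grade 1 "Blisters or ulcers at injection site, diameter <1 cm"; Grade 2 "Blisters or ulcers at injection site, diameter 1–2 cm, heals within 2 weeks"; Grade 3 "Blisters or ulcers at injection site, does not heal for over 2 weeks"; Grade 4 is necrosis. Pustules at the DNA site are Grade 1 below 0.5 cm, Grade 2 at "Diameter 0.5–1 cm", and Grade 3 at "Diameter >1 cm, no tendency to heal for 2 weeks".

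Under systemic symptoms, vomiting is Grade 2 at 2 to 5 episodes and Grade 3 at ">6 episodes in 24 hours or IV fluids required". Diarrhoea is Grade 2 at 4 to 5 episodes a day (or lasting over a week) and Grade 3 above 6 a day or with other listed signs.

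Section 6.5.1 says that blisters, ulcers and pustules are graded on size among other features. Section 6.5.4 supplies the fallback: "For clinical abnormalities not covered in Appendix 2, the severity will be assessed using the grading standards provided in Table 8".

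The grades are used in five places. Section 6.2.1.1 makes Grade 3 or higher reactions the primary safety endpoint. Section 6.2.2 counts Grade 1 and 2 events. Sections 6.5.8 and 6.7.1 stop the individual's vaccination at a related Grade 3 event. Sections 6.4.2 and 6.7.2 halt vaccination at three or more related events of Grade 3 or higher. Section 6.4.2 also places the low-dose safety assessment within two weeks of each DNA vaccination.

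**The concern.** A toxicity scale that feeds an endpoint and a stopping count should assign one grade to every possible reaction, and the grade should not fall as the reaction grows. In these rows neither holds: as size or episode count rises past the Grade 2 ceiling, the printed grade disappears. The investigator must then decide whether the event is Grade 2, Grade 3 or something taken from Table 8. DNA-site reactions are part of the safety comparison of 2 mg with 4 mg, and the halt turns on a third event in a subgroup of 12, so an undefined grade leaves a consequential count to judgement.

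The pattern looks like a drafting slip. DNA-site erythema, induration, papules and swelling all reach Grade 3 on size alone above 3 cm, as do rTV-site blisters and pustules. Only the DNA-site blister/ulcer and pustule rows lack that route.

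**Working it through.** The plan states no figure to reproduce. The check applies the Annex 2 rows as printed.

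**1. Grade by size and healing time.** Let d be the diameter in cm and h the days to healing.
- Blister/ulcer: Grade 1 if d < 1; Grade 2 if 1 ≤ d ≤ 2 and h ≤ 14; Grade 3 if h > 14.
- Pustule: Grade 1 if d < 0.5; Grade 2 if 0.5 ≤ d ≤ 1; Grade 3 if d > 1 and h > 14, taking h > 14 as the meaning of no healing tendency for 2 weeks.
- Where two grades fit, the higher is taken. This is an assumption: a blister under 1 cm unhealed after 2 weeks meets both Grade 1 and Grade 3.

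| d (cm) | 0.4 | 0.8 | 1.5 | 2.0 | 2.5 | 5 |
|---|---|---|---|---|---|---|
| Blister, heals day 10 | 1 | 1 | 2 | 2 | none | none |
| Blister, heals day 20 | 3 | 3 | 3 | 3 | 3 | 3 |
| Pustule, heals day 10 | 1 | 2 | none | none | none | none |
| Pustule, heals day 20 | 1 | 2 | 3 | 3 | 3 | 3 |

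**2. Grade by count.** Vomiting: 5 episodes = Grade 2, 6 = none, 7 = Grade 3. Diarrhoea on frequency alone gives the same: 5 = Grade 2, 6 = none, 7 = Grade 3.

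**3. What reaches the Grade ≥3 counts.** Recode each row as 1 if the grade is 3 or more and 0 otherwise. Blister healing day 10: 0 throughout. Blister healing day 20: 1 throughout. Pustule healing day 10: 0 throughout. Pustule healing day 20: 0, 0, 1, 1, 1, 1. Vomiting, 1 to 8 episodes: 0, 0, 0, 0, 0, 0, 1, 1. At fixed healing time none of these sequences falls. The drop is from Grade 2 to no grade.

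**4. The fallback.** Table 8 grades by duration of discomfort, limitation of activity and need for treatment. The Other Discomfort row of Annex 2 uses activity and medication. Neither uses size or count. It is also unclear whether a reaction that Annex 2 lists by name, but not at that size, falls under Section 6.5.4 at all. A blister lasting 10 days without limiting activity is too long for Table 8 Grade 1 (under 48 hours) and does not show the limitation described for Grade 2.

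**5. Timing.** A lesion that appears on the day of vaccination (day 0) can be known to have gone more than 14 days unhealed only from day 15. The low-dose look ends at day 14. Since 15 > 14, Grade 3 for a blister or ulcer cannot be established inside it, whatever the size; only necrosis (Grade 4) can. Grade 3 for a pustule needs 2 weeks without healing and is at best borderline.

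**6. Illustration with assumed rates.** Suppose 12 low-dose participants have at most one event each, with probability p of an event meant to be Grade ≥3, and a share g of such events goes uncounted. With q = p(1 − g), P(3 or more counted) = 1 − Σ(k = 0 to 2) C(12, k) q^k (1 − q)^(12 − k).

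| p | g = 0 | g = 25% | g = 50% |
|---|---|---|---|
| 0.10 | 0.111 | 0.056 | 0.020 |
| 0.20 | 0.442 | 0.264 | 0.111 |
| 0.30 | 0.747 | 0.528 | 0.264 |

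Neither p nor g is in the protocol, and g could be close to zero. The table shows only how sensitive a three-event rule is to uncounted events.

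**The case against.** Much can be said in the protocol's defence. Section 6.5.6 has the head of the clinical trial unit review every grade, so an unlisted combination would be judged, not lost. Grading by healing time is a legitimate severity criterion, and a small unhealed ulcer may properly outrank a larger healed one. The gastrointestinal gap is a single integer; intravenous fluids (vomiting), or bloody stools, electrolyte imbalance or duration over a week (diarrhoea), still assign a grade. The other DNA-site size bands are contiguous. On timing, Sections 6.5.8 and 6.7.2 carry no two-week limit and there is a visit at week 4 after each DNA dose, so a late Grade 3 can still be recorded. All of this stands and keeps the effect narrow. It does not fill the gaps: review without a criterion is discretion, and Section 6.5.1 says size should count.

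Three stronger readings are tempting and not supported.
- A reader might infer that larger reactions score lower in the primary endpoint and halting counts. Step 3 shows that, at equal healing time, they never do.
- A reader might infer from the urine glucose row, where Grade 1 is 15 mmol/L or less with no floor, that every normal urine is a Grade 1 event. Section 6.5.5 grades abnormal results only, and Section 6.5.6 defines adverse events as unfavourable or unintended. What remains is a missing lower bound, which cannot reach the Grade ≥3 counts.
- A reader might infer that Table 8 makes any large blister that does not limit activity Grade 1. That grade also requires discomfort under 48 hours and no medical treatment.

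**Conclusion.** The point holds in limited form. Four rows (DNA-site blisters/ulcers, DNA-site pustules, vomiting, diarrhoea) have no stated grade just above the Grade 2 ceiling. The direct distortion is in the secondary Grade 1–2 endpoint, where a larger reaction can drop out while a smaller one is counted. For the primary endpoint, individual discontinuation and the three-event halt, the fault is an undefined classification, not a reversed one. The low-dose look and the Grade 3 blister/ulcer criterion are inconsistent in time and need reconciling.

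The size cannot be quantified from the protocol, which gives no rate for these reactions. The conclusion rests on reading the rows as printed and on taking the higher grade where two apply. It does not depend on the assumed rates in step 6. The protocol does not show which cut points were intended. This is worth correcting before the first dose; it does not call the design into question.

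**What to change.** Before the first dose, revise the four Annex 2 rows so that they are contiguous and mutually exclusive, cover every size, healing time and episode count, and give grades that do not fall as size or count rises. The sponsor chooses the cut points.

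Reconcile the revised rows with Section 6.5.1 (size as a grading feature), Section 6.5.4 (state whether Table 8 applies to a listed reaction at an unlisted size or count) and Section 6.4.2 (timing of the low-dose assessment against the healing-time criteria).

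As a minor clarification, state a lower bound for Grade 1 urine glucose, as the neighbouring protein and red-cell rows already do.

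The cost is about one page of annex text and the matching case report form edit checks; no new data are needed.

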#### **6.2.1 Primary Endpoint Events**

##### **6.2.1.1 Primary Safety Endpoint Event**

During the clinical trial, the safety indicators are graded according to Annex 2, and the following are the primary safety endpoint events:

- (1) Grade 3 or higher local adverse reactions;
- (2) Grade 3 or higher systemic adverse reactions;
- (3) Any events of immunization regimen termination caused by vaccine problems;
- (4) Any event leading to the discontinuation of the immunization schedule due to vaccine-related issues.

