#### **6.2.2 Secondary Endpoint Events**

Information on secondary safety and immunogenicity endpoints will be collected according to the following criteria:

- (1) All Grade 1 and 2 adverse events occurring within 4 weeks after each vaccination;
- (2) The following responses will be measured at 2, 4, 8, 12, 16, 20, and 24 weeks after

the last vaccination:

- Titers of HIV total antibodies, Env, Gag binding antibodies, and HIV neutralizing antibodies;
- Proportions of HIV-specific cytokines such as IFN- $\gamma$  and IL-2;
- Binding antibody titers against vaccinia virus following rTV immunization.

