### 6.5.1 Evaluation of Local Adverse Events

Local adverse events will be evaluated according to the criteria outlined in Appendix 2, with the following explanations:

1. Pain at the vaccination site: This will be recorded by the participants themselves.
2. Skin erythema, swelling, papules, or induration at the injection site: These will be graded based on the maximum diameter of the reaction and its duration.
3. Blisters or ulcers: These will be graded based on their size, depth, healing time, nature of the blister (e.g., whether it is bloody), duration, and whether necrosis occurs.
4. Pustules: These will be graded based on their size, duration, and whether necrosis occurs.
5. Generalized rash: This will be graded based on the number of papules, presence of itching, exudation, and other characteristics.

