The grading of adverse events will be determined after review by the head of the clinical trial unit. The relationship between adverse events and vaccination will be preliminarily assessed by the researchers at the clinical trial unit, but the final determination will be made through discussion between the sponsor and the clinical trial unit and confirmed in writing.

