### 6.5.7 Report of Adverse Events

All adverse events must be recorded in the Case Report Forms (CRFs) and entered into the database. The records should include a general description of the symptoms and signs, the dates of onset and resolution, severity, relationship to the investigational vaccine or other medications, and measures taken to alleviate the symptoms.

If a participant experiences a serious adverse event (SAE) during the clinical trial, the investigator must immediately provide appropriate treatment to the participant.

Simultaneously, the investigator must complete a Serious Adverse Event Report Form (see Appendix 8) and report the event to the Safety Supervision Department of the National Medical Products Administration (NMPA) within 24 hours, with copies sent to the Registration Department, the sponsor, the ethics committee, and the higher-level health administration authorities. The report must include the rationale for diagnosing the event as an SAE and be signed and dated by the investigator. Grade 3 adverse events must be reported to the clinical trial sponsor within 2 working days after the decision is made.

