|                    | Generalized Rash                             | Scattered maculopapular rash (<5 areas), no itching or other symptoms | Scattered macules or papules (>5 areas), itching or other symptoms, no treatment required | Diffuse macules or papules, or exudative rash, requires medication   | Rash involving mucous membranes, exfoliative dermatitis, or erythema multiforme, or Stevens-Johnson syndrome |
| rTV vaccine | Injection Site
Papules                    | Diameter 1.1–1.5 cm                                                   | Diameter 1.6–3 cm                                                                         | Diameter >3 cm                                                       |                                                                                                              |
|                    | Injection Site or
Swelling
Redness     | Diameter 3–5 cm                                                       | Diameter 5.1–10 cm, improves within 5 days                                                | Diameter 5.1–10 cm, persists for over 5 days, or diameter >10 cm     |                                                                                                              |
|                    | Injection Site
Induration                 | Diameter 1.1–1.5 cm                                                   | Diameter 1.6–3 cm                                                                         | Diameter >3 cm                                                       |                                                                                                              |
|                    | Injection Site
Blisters                   | Diameter 1.1–1.5 cm                                                   | Diameter 1.6–3 cm                                                                         | Diameter >3 cm                                                       |                                                                                                              |
|                    | Injection Site
Pustules                   | Diameter 1.1–1.5 cm                                                   | Diameter 1.6–3 cm                                                                         | Diameter >3 cm                                                       | Pustules continue to expand without scabbing after 2 weeks; gangrene or exfoliative dermatitis               |

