|                   | Injection Site
Erythema                         | Diameter <1.5 cm                                                                  | Diameter 1.5–3 cm                                                                                                     | Diameter >3 cm                                                 | Gangrene or exfoliative dermatitis |
|-------------------|----------------------------------------------------|-----------------------------------------------------------------------------------|-----------------------------------------------------------------------------------------------------------------------|----------------------------------------------------------------|------------------------------------|
| Systemic Symptoms |                                                    |                                                                                   |                                                                                                                       |                                                                |                                    |
| Headache          | Does not affect activity, no treatment required    | Transient, affects daily activities, requires treatment (non-narcotic analgesics) | Severely affects daily activities, occasional narcotic treatment required                                             | Persistent, requires repeated narcotic treatment               |                                    |
| Chills            | Occasional OTC non-steroidal antipyretics required | Limits daily activities >6 hours, or requires repeated non-steroidal antipyretics | Severely affects daily activities, requires prescription medication                                                   | Hospitalization required                                       |                                    |
| Fatigue           | Reduced normal activity <48 hours                  | Reduced normal activity 20%–50% >48 hours                                         | Severely affects daily activities, reduces normal activity >50%, unable to work                                       | Unable to care for self, emergency or hospitalization          |                                    |

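### Annex 2 grades redness after rTV on two conflicting rows, so the same reaction can be Grade 1 or Grade 3, or Grade 2 or Grade 3

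*Protocol*

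**What the plan says.** Section 6.2.1.1 grades safety by Annex 2 and makes "Grade 3 or higher local adverse reactions" a primary safety endpoint event.

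The rTV vaccine block of Annex 2 contains two rows that bear on redness:

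- **Swelling or Redness.** Grade 1 is 3–5 cm. Grade 2 is 5.1–10 cm improving within 5 days. Grade 3 is "Diameter 5.1–10 cm, persists for over 5 days, or diameter >10 cm". The Grade 4 cell is empty.
- **Erythema**, the last row before Systemic Symptoms. Grade 1 is below 1.5 cm, Grade 2 is 1.5–3 cm and Grade 3 is above 3 cm, with no duration condition. Grade 4 is "Gangrene or exfoliative dermatitis".

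The DNA vaccine block has its own "Injection Site Erythema" row with the same limits and the same Grade 4 text.

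On how to grade, Section 6.5.1 says of erythema, swelling, papules and induration: "These will be graded based on the maximum diameter of the reaction and its duration". Section 6.5.6 adds: "The grading of adverse events will be determined after review by the head of the clinical trial unit". Section 6.5.8, item 4, refers reactions after rTV to Annex 6, which describes a red halo as typical on days 5–6 but gives no diameter for it.

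**The concern.** Erythema and redness are the same sign, yet the two rows put Grade 3 at very different sizes. The grade feeds several rules:

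- **Primary safety endpoint (6.2.1.1, Table 3).** The proportion with Grade 3 or higher events after rTV would depend, for this sign, on the row the grader happened to use.
- **Reporting (6.5.7).** "Grade 3 adverse events must be reported to the clinical trial sponsor within 2 working days after the decision is made"
- **Subject-level rules (6.5.8, 6.7.1).** A vaccine-related Grade 3 local event stops immunization and ends participation early, with follow-up continued where possible.
- **Study-level rule (6.7.2).** Three or more related Grade 3 or higher events after a vaccination in the low-dose group stop later vaccinations in all groups. Short fever is the only exclusion.
- **Secondary endpoint (6.2.2).** "All Grade 1 and 2 adverse events occurring within 4 weeks after each vaccination" would include redness below 3 cm on one row and not on the other.

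Graders would also choose the row knowing the allocation. Clinical observers are unblinded on day 3 after rTV (6.4.3, 6.10.4), before the typical halo appears on days 5–6 (Annex 6).

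**Working it through.** The plan states no figure to reproduce. The check sets the two rows side by side, then shows what a difference could mean.

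**1. Grade by row**

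| Redness after rTV | Swelling or Redness row | Erythema row | Agree? |
|---|---|---|---|
| below 1.5 cm | no grade | 1 | no |
| 1.5 cm to below 3 cm | no grade | 2 | no |
| exactly 3 cm | 1 | 2 | no |
| above 3 cm to 5 cm | 1 | 3 | no |
| 5.1–10 cm, improves within 5 days | 2 | 3 | no |
| 5.1–10 cm, lasts over 5 days | 3 | 3 | yes |
| above 10 cm | 3 | 3 | yes |

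The Grade 3 cell of the Swelling or Redness row is the region of agreement. The conflict lies between that row's Grade 1 and Grade 2 cells and the above-3 cm cell of the Erythema row.

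**2. Does another section choose the row?**

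- Section 6.5.1 mentions diameter and duration, but one sentence covers four signs and most of their Annex 2 rows use diameter alone. It also uses the word erythema, which is the label of the other row.
- Section 6.5.6 names who reviews the grade but gives no rule.
- Annex 6 gives no diameter.

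**3. Illustrative size.** Let p be the share of rTV recipients whose redness falls in the two ranges where one row gives Grade 3 and the other does not. The documents give no value for p, so the values below are assumptions that show direction only. Table 5 gives 24 rTV recipients, 12 of them low-dose.

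- Expected participants moved to Grade 3 by the Erythema row: 24 × p.
- Chance of reaching the 6.7.2 count in the low-dose group, with one related event per participant: P(Bin(12, p) ≥ 3).

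| p | 24p | P(Bin(12, p) ≥ 3) |
|---|---|---|
| 0.05 | 1.2 | 0.020 |
| 0.10 | 2.4 | 0.111 |
| 0.20 | 4.8 | 0.442 |
| 0.50 | 12.0 | 0.981 |

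On the Swelling or Redness row the same reactions contribute 0 to both columns.

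**4. Can the 6.7.2 count still matter after rTV?** Table 5 puts low-dose rTV at week 12 and the second cohort's rTV or rTV placebo at week 14. Annex 6 has the local reaction peaking on days 8–10, so a count reached after the week-12 dose could stop the week-14 dose.

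**5. Can the disputed range be reached?** Each recipient has two prick sites on one arm, 2 cm apart (2.4, Table 5 note 2). With centres 2 cm apart, circular halos of diameter d touch at d = 2 cm and together span 2 + d, which is 4 cm at that point. If the 2 cm is edge to edge between two 5 mm prick areas, the centres are 2.5 cm apart and the span at contact is 2.5 + 2.5 = 5.0 cm. Either span is Grade 1 on one row and Grade 3 on the other. The protocol does not say whether joined redness is measured as one reaction.

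**The case against.** **The rows may not conflict.** The Erythema row follows a page break with a blank vaccine cell, and its limits equal the DNA row, so it may be a stray copy. This uncertainty stands. But the row follows rTV Pustules and precedes Systemic Symptoms, and the DNA block already has an Erythema row. A DNA-only reading would leave a misplaced duplicate, which also needs correcting. The two rows might also have been meant for different signs, one mainly for swelling. With redness named in the first row, that split is not what the annex says.

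**Section 6.5.1 favours one row.** Among the rows for the signs in that sentence, only the rTV Swelling or Redness row uses both diameter and duration. This is a fair hint, and a single hospital with one reviewer of grades limits inconsistency between raters. It is still not a precedence rule.

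**The consequences are thin.** This is largely right. rTV is the last scheduled dose, so the immunization stop matters only for someone due for re-administration under 6.4.3. That requires no pustule and no antibody response, and such a person is unlikely to have wide redness. The safety analysis is mainly descriptive. The endpoint count, the 2-day report and the possible effect on week-14 doses remain.

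**The larger scenarios are implausible.** The Synopsis reports expected local reactions in all 12 Phase Ia subjects and no vaccine-related event of Grade 3 or higher. If the Erythema limit was used there, 0 of 12 has probability 0.5^12 = 0.0002 at p = 0.5 and 0.8^12 = 0.07 at p = 0.2. The protocol also expects milder reactions than those of the parent strain. This tempers the upper rows of the illustration. It does not settle them, because neither the Phase Ia redness sizes nor the row used are given.

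**Conclusion.** The concern holds. As Annex 2 reads, redness after rTV above 3 cm and up to 5 cm is Grade 1 or Grade 3, and redness of 5.1–10 cm improving within 5 days is Grade 2 or Grade 3. Nothing elsewhere in the protocol resolves it. The conclusion rests on two readings: that the Erythema row belongs to the rTV block, and that redness and erythema are the same sign.

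The effect on the primary safety endpoint is real in direction but of unknown size. It is confined to redness at the rTV site; DNA-site reactions, other rTV local signs and systemic events are untouched. This should be fixed before dosing, with moderate confidence, because a later choice of row would be made with the reactions and the allocation known.

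**What to change.** Before first dosing, replace the two rows with one rTV redness scale, set by the clinical team, that covers every diameter and Grade 4. One option has three parts:

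- keep the Swelling or Redness limits;
- carry over the Erythema row's Grade 4 criterion;
- state that redness below 3 cm is an expected, ungraded reaction, or give its grade.

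State whether redness joining the two prick sites is measured as one reaction. Point Section 6.5.1 and the CRF check to that row. Record maximum diameter and duration for every reaction, so that it can be regraded.

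The cost is one merged annex row, one cross-reference and one CRF check, with no change to sample size, visits or assays. The option above has two drawbacks: it adopts the more lenient Grade 3 limit, and if redness below 3 cm is left ungraded it drops out of the Grade 1–2 secondary endpoint.
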